#### Secondary outcomes

The secondary objectives of this study are to evaluate accuracy, implant density, radiation exposure and various other measures of surgical and postsurgical success.

#### Secondary outcomes related to accuracy

Pedicle screw intraoperative revision ratesIntraoperatively revised based on clinical assessment.Intraoperatively revised based on neurophysiology.Intraoperatively revised based on intraoperative verification CBCT scan.Technical accuracy for ARSN and IRSN, defined as:Deviation from planned navigation path in mm at bone entry and screw tip measured on the postoperative computed tomography (CT).Angular deviation of the placed screw compared to planned navigation path measured on the postoperative CT.Accuracy at 1 st attempt = (screws placed at first attempt according to intraoperative protocols and graded 0 or 1)/(total number of placed screws). Assessed on intraoperative CBCT.The secondary endpoint, Final accuracy of placed pedicle screws, is calculated as: number of accurately placed screws (Gertzbein grade 0 or 1) according to postoperative CT/total number of placed screws.

#### Secondary outcomes related to implant density

Pedicle screw placement density comparison. The study aims for 100% pedicle screw density. Hooks may be placed as rescue or if screw placement fails.Final implant density compared to planned 100% pedicle screw density.Pedicle screw density.Hook density.Morphometric measurement for regression analysis.Pedicle diameters are measured on preop CT.Deformity correction rate.Cobb angle improvement.

#### Secondary outcomes related to radiation dose exposure

The following objectives will be measured by estimates from the CBCT systems in the operating theatres (estimated by dose area product/kerma area product, radiation time, computed tomography dose index) and dosimeters.Patient radiation exposure (ED in mSv) for the whole procedure.Patient radiation exposure (ED in mSv) for fluoroscopy.Patient radiation exposure (ED in mSv) for each CBCT.Average staff radiation exposure (in Sv) for the whole procedure.

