### Randomization and blinding

The subjects are randomized in a 1:1 ratio, with stratification for operating theatre since the IRSN or ARSN system are located in different operating theatres. Randomization will take place intraoperatively after completed surgical exposure of the posterior elements and will be performed through the web-based platform of the Swespine registry using an allocation sequence hidden from the healthcare staff. Block randomization will be used. Block sizes will be unknown for the researchers.

The study design does not allow blinding of the surgeon. Since the primary outcome is assessed at the time of surgery and a short time thereafter, we do not find it necessary to blind the patient.

Intraoperatively, CBCT verification scans will be assessed by the surgeon to make decisions on screw revision. However, all radiological image analyses, on both intra- and postoperative imaging will be performed postoperatively by blinded reviewers.

Patient reported outcomes will however be assessed without influence of the care giver.

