#### Augmented reality surgical navigation

After standard exposure of the region of interest of the spine a cone beam CT (CBCT) (Philips Allura, Philips, Best, The Netherlands) of the area is performed. Navigation is based on the recognition of optical markers (fiducials) on the skin by the equipment during the CBCT and navigation [12, 18, 19]. The CBCT will result in a three-dimensional image of the spine in which screws are placed virtually on a computer screen. Navigation then takes place. The navigation will show the entry point and direction of the planned screws on an augmented reality image screen in the operating theatre [14, 20, 21]. After placement of the screws, the positioning is checked with a second CBCT. Misplaced screws may be repositioned or extracted.

After screw placement, rods are placed, correction of the deformity and fusion are performed, and the wound is closed.

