### Infrared surgical navigation

After standard exposure of the region of interest of the spine a CBCT of the area is performed using the O-arm (Medtronic, Minneapolis, Minnesota, USA) and Universal Air (Brainlab spinal navigation system, Brainlab AG, Munich, Germany). Navigation is based on the recognition of optical markers on a dynamic reference frame attached to a bony prominence of the spine (Brainlab). Navigation requires detection of the optical markers through infrared light and that the reference frame is tightly fixed to the spine. The CBCT will result in a three-dimensional image of the spine in which screws are placed virtually on a computer screen. After placement of the screws, the positioning is checked with a second CBCT. Misplaced screws may be repositioned or extracted [22].

After screw placement, rods are placed, correction of the deformity and fusion are performed, and the wound is closed.

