### Free hand

After standard exposure of the region of interest of the spine screws are placed based on anatomical landmarks and feeling of intact bony canals made in the pedicle [14]. If needed, fluoroscopy is performed to check the planned screw paths. After placement of the screws, the positioning is checked with a cone beam CT (O-arm or Philips Allura). Misplaced screws may be repositioned or extracted. After screw placement, rods are placed, correction of the deformity and fusion are performed, and the wound is closed.

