#### Sample size for secondary objectives

Potentially the difference in intraoperative radiation could be two-fold when comparing navigated and free hand groups. The study will be sufficient to identify differences down to 20% between navigated and free hand when the navigated and free hand groups are pooled with a power of 80%, alpha = 0.05.

Minimal clinical important difference for SRS-22r is around 0.4. With a power of 80%, alpha = 0.05, a sample size of 37 patients in each group would be required to detect such a difference. Pooling data from the navigated and control groups will be done and sample size sufficient with an estimated 44 patients in the navigated and free hand groups, respectively.

Operative times will be compared between navigated and free hand groups. However, the current study sample size is underpowered to identify any differences in operating time when using our own earlier data with 403 (101) minutes and 361 (150) minutes in the navigated and free hand group respectively [14]; sample size needed would be 147 patients in each group. The data obtained in the current study may therefore only be indicative.

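### Patient radiation dose: ARSN v IRSN cannot be separated from the imaging system, so comparisons with free hand should be made within theatre

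*Protocol article*

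**What the plan says.** Under Secondary outcomes related to radiation dose exposure, the protocol article lists patient effective dose for the whole procedure ("Patient radiation exposure (ED in mSv) for the whole procedure"), for fluoroscopy and for each CBCT. The sources are the outputs of the CBCT systems ("estimated by dose area product/kerma area product, radiation time, computed tomography dose index") and dosimeters. Table 2 assigns dosimeters to staff radiation and the imaging equipment to patient radiation.

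The imaging system depends on the arm:
- ARSN: "a cone beam CT (CBCT) (Philips Allura, Philips, Best, The Netherlands) of the area is performed".
- IRSN: "a CBCT of the area is performed using the O-arm".
- Free hand: "the positioning is checked with a cone beam CT (O-arm or Philips Allura".

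Randomization is 1:1, "with stratification for operating theatre since the IRSN or ARSN system are located in different operating theatres". Study outcomes and variables plans ARSN v free hand, IRSN v free hand and ARSN v IRSN for primary and secondary outcomes alike. Statistical analysis names ordinary two-group and multi-group tests and does not mention theatre. The only power statement for radiation concerns the pooled groups: "The study will be sufficient to identify differences down to 20% between navigated and free hand".

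**The concern.** Effective dose is not read off a scanner. It is derived from recorded quantities by some conversion. If the conversion for one system runs systematically higher than for the other, every patient imaged on that system carries the same offset. In ARSN v IRSN all patients in one arm carry it and none in the other, so it appears in full as an effect of technique, and a larger sample only makes it more significant.

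A weaker form can affect the comparisons with free hand. If all free-hand patients serve as controls for ARSN, about half were imaged on the other system, and about half of the offset remains in the contrast.

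The Introduction names radiation as one of the trial's three main domains, so a spurious difference between two commercial systems would be read as a main result.

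**Working it through.** **The plan's own figure.** The article claims 80% power at alpha 0.05 for a 20% difference between pooled groups of 44 and 44. It gives no standard deviation, so the claim can be neither confirmed nor refuted. It can be turned into the CV that it implies:

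- Two-sided: standardised difference = (1.960 + 0.842) × √(2/44) = 0.597, so CV = 0.20/0.597 = 0.335.
- One-sided: (1.645 + 0.842) × √(2/44) = 0.530, so CV = 0.20/0.530 = 0.377.

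A CV of 0.335 is therefore a reasonable central value. Values of 0.20 and 0.50 show the range.

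**Layout.** With 22 patients per group, 44 free-hand patients and 1:1 allocation stratified by theatre, I take 22 ARSN and 22 free hand in the Allura theatre, and 22 IRSN and 22 free hand in the O-arm theatre.

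**What an offset does.** Let doses be log-normal with no true difference anywhere, and let every dose estimated on one system be multiplied by (1 + b). On the log scale the shift is ln(1 + b). The expected contrasts are:

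- ARSN v IRSN: ln(1 + b), the whole offset.
- ARSN v free hand in the same theatre: ln(1 + b) − ln(1 + b) = 0.
- ARSN v all 44 free hand: ln(1 + b) − ½ ln(1 + b) = ½ ln(1 + b).
- Pooled navigated v pooled free hand: ½ ln(1 + b) − ½ ln(1 + b) = 0.

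**Rejection rates.** Two-sided t-tests at 0.05 in 20,000 simulated trials per setting. The offsets are assumptions.

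| CV | Comparison | b = 10% | 20% | 30% | 50% |
|---|---|---|---|---|---|
| 0.20 | ARSN v IRSN | 34.2% | 84.5% | 99.1% | 100.0% |
| 0.20 | ARSN v all free hand | 13.6% | 36.0% | 60.1% | 90.2% |
| 0.20 | ARSN v free hand, same theatre | 4.8% | 4.9% | 5.1% | 4.6% |
| 0.20 | Pooled navigated v free hand | 4.5% | 3.0% | 1.8% | 0.5% |
| 0.335 | ARSN v IRSN | 15.3% | 44.3% | 74.6% | 98.2% |
| 0.335 | ARSN v all free hand | 8.4% | 17.1% | 29.1% | 55.9% |
| 0.335 | ARSN v free hand, same theatre | 5.0% | 5.2% | 4.5% | 5.0% |
| 0.335 | Pooled navigated v free hand | 4.9% | 4.1% | 3.4% | 2.0% |
| 0.50 | ARSN v IRSN | 9.9% | 23.6% | 43.5% | 79.1% |
| 0.50 | ARSN v all free hand | 6.4% | 10.5% | 16.8% | 31.7% |
| 0.50 | ARSN v free hand, same theatre | 5.2% | 5.3% | 5.2% | 4.9% |
| 0.50 | Pooled navigated v free hand | 4.8% | 4.6% | 4.3% | 3.4% |

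IRSN v all free hand agrees with the ARSN rows to within 1 percentage point. A t-test power calculation on the untransformed scale, with standardised shift b/CV, CV 0.33 and 22 per arm, gives 17%, 50% and 84% for ARSN v IRSN at 10%, 20% and 30%. That is the source of the 44-50% range at 20%.

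The pooled test falls below 5% because the offset adds spread within both groups without moving their means apart.

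**The case against.** The case against has real weight.

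- *The list of dose quantities.* A reader might infer that the article treats dose area product, CTDI and radiation time as interchangeable routes to mSv, or that time alone is converted to a dose. It says neither. It lists recorded quantities for several outcomes, and different quantities for different acquisitions is just as natural a reading.
- *The conversion method.* How each output becomes mSv is detail that a condensed article may leave to the full protocol or SAP. Its absence is not a fault, and a harmonised conversion may already be planned.
- *The 20% claim.* A reader might infer that an offset of 20% would by itself produce the difference the trial says it can detect. That claim concerns pooled navigated v pooled free hand, where stratification by theatre makes the offset cancel.
- *Radiation results in general.* A reader might infer that all of them are compromised. Same-theatre comparisons hold their level, and staff dose comes from dosimeters and is outside this point.

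All four stand. They leave two things untouched. Technique and system coincide in ARSN v IRSN by design, whatever the unseen documents say. And the comparisons with free hand, as described, are not tied to theatre. A true dose difference between the scanners is part of each technique as delivered and is legitimate to report. A conversion difference is not, and ARSN v IRSN cannot tell the two apart.

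**Conclusion.** The point holds for two contrasts in patient effective dose. ARSN v IRSN is completely confounded with imaging system. ARSN v free hand and IRSN v free hand are partly exposed, but only if free-hand patients from both theatres are pooled without regard to theatre; the article does not say whether they will be.

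The size is unknown. The central illustration, a 20% offset with a CV near 0.33, rests on an assumed offset, on a CV inferred from the power statement, and on free hand being balanced over theatres. The same 20% offset gives anything from about 24% (CV 0.50) to 85% (CV 0.20) false positives in ARSN v IRSN.

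Exact cancellation within theatre also assumes that the offset is the same proportion in both arms. Navigated patients have two CBCTs, and free-hand patients one plus fluoroscopy if needed. If conversion error differs between CBCT and fluoroscopy, cancellation in whole-procedure dose is approximate.

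This concerns a secondary outcome and is a low-cost improvement, not a flaw in the trial's main analysis.

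**What to change.** - Analyse patient dose for ARSN v free hand and IRSN v free hand within the same theatre and imaging system, or stratified by theatre as randomised.
- Base the radiation conclusion on these comparisons and on the pooled navigated v free-hand comparison stratified by theatre.
- Report ARSN v IRSN dose as system-dependent, with a sensitivity range for the conversion between systems.
- Report radiation time descriptively.

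The cost is wording and a little analysis. Each within-theatre comparison has about 22 controls, not 44. At a CV of 0.335 and a true 20% difference, by the normal approximation:

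- 22 v 44: 0.597/√(1/22 + 1/44) − 1.960 = 0.33, power about 63%.
- 22 v 22: 0.597/√(2/22) − 1.960 = 0.02, power about 51%.

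The pooled comparison keeps its 44 v 44. The ARSN v IRSN dose statement becomes more cautious.

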### Inclusion criteria

• Written informed consent.

• Age 12 years and older.

• Spinal deformity surgery.

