#### Secondary outcomes related to surgical and postsurgical parameters

Patient reported outcome measures:oThe SRS-22r is a scoliosis specific questionnaire aiming to estimate quality of life in patients with scoliosis [24]. It contains 24 items divided into 5 domains covering function, pain, self-image, mental health, and satisfaction. An index value is calculated for each domain and a total index value is possible to calculate ranging from 1 (worst) to 5 (best). SRS-22r will be collected from Swespine.oEOSQ-24 is a proxy answered questionnaire and will be used in individuals up to the age of 15. It consists of 24 questions of daily function, pain, pulmonary function and mobility [25]. EOSQ-24 will be collected from Swespine.oOswestry Disability index (ODI). ODI is a back specific index measuring disability due to back pain [26]. It is the recommended instrument for studies concerning back pain. An index from 0–100 is calculated. An ODI of 0–20 indicate minimal disability, 21–40; moderate disability, 41–60; severe disability, 61–80; severely crippled, 81–100; bed-bound. ODI will be collected from Swespine.oEQ-5D 3 level is a generic quality of life instrument and consists of five areas reflecting mobility, self-care, usual activities, pain/discomfort and anxiety/depression [27]. Response alternatives range from no problems to extreme problems. An index can be calculated and depending on baseline value set used the index runs between approximately −0.5 (worst possible health) to 1.0 (best possible health). The EQ-5D-3L will be used for health economic analyses. The EQ-VAS is part of the EQ-5D and registers the patient’s self-rated health on a visual analogue scale (from 0 to 100; best). EQ-5D-3L will be collected from Swespine.Total procedure time as well as normalized to number of spinal levels from the upper to the lower instrumented vertebra.Intraoperative planning time (from start of planning in navigation software until last screw planned) (only when treated with ARSN or IRSN).Instrumentation time (total time for navigated/FH screw placement from first to last screw placement).Instrumentation time normalized to number of levels.Time for intraoperative verification imaging (CBCT and/or Fluoroscopy).Screw placement time (per screw, from owl to screw placed).Intraoperative blood loss.Intraoperative complications.Length of hospital stays.Administered doses of analgesia and types of analgesic medications required.Complications: at discharge, 30-, and 90-days.Readmissions and reasons for revision surgery: at 30-, 90-days, and 1-year.Costs per patient: at discharge, 30-, 90-days, and 1-year.

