### Statistical analysis

In order to evaluate hypotheses of variables in contingency tables, the Chi-square or Fisher's Exact Tests will be used as appropriate. In order to test differences in continuous variables measured on at least interval scale between two independent groups the Student’s t-test for uncorrelated means will be used. The non-parametrical Mann–Whitney test will be used to test ordinal data. Regression analysis will be used to evaluate the dependency between variables and the Pearson correlation coefficient will be used in order to test independence between variables. In addition to that descriptive statistics will be used to characterize the data; means and 95% confidence intervals will be used for parametric data, medians and interquartile ranges for non-parametric data, and number (proportions) for categorical data. In case of multiple groups comparison. ANOVA, Kruskal–Wallis, and Chi-squared tests will be used respectively, along with post hoc analysis.

Protocol deviations will be recorded transparently. However, data from the different groups will be compared based on the'intention to treat'principle. An intention to treat (ITT) analysis means that all patients, regardless of treatment change, loss to follow-up or drop-out, remain in the analysis of the group to which they were randomized.

Statistical expertise will perform the statistical analysis.

Patient reported outcome measures consisting of ordinal scales for the different indices, will be compared using the Mann–Whitney test.

Data on total time on sick leave as well as the diagnosis used for sick leave will be collected.

Data on analgesic and antibiotic use will be collected from hospital files. Since different opioids may be used, conversion to morphine equivalents may be done. Data on other analgesics will be collected. Data on costs for the prescribed pharmaceuticals will be collected. Total amount of collected opioids (continuous data consisting of morphine equivalents) will be compared with the Student’s t-test or the Mann–Whitney test, depending on distribution.

Adverse events will be collected during the follow-up and classified as minor or major [30]. Data will be analyzed as dichotomous variables with Chi-square or Fisher tests.

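### Patient radiation dose is set for an unadjusted comparison in raw mSv, which probably gives up precision that age and planned construct length could recover for the 20% target

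*Protocol article*

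**What the plan says.** The Introduction of the protocol article names intraoperative radiation as one of three main study domains. Under Secondary outcomes related to radiation dose exposure, patient dose appears in three forms: "Patient radiation exposure (ED in mSv) for the whole procedure", the same for fluoroscopy, and "Patient radiation exposure (ED in mSv) for each CBCT". None is scaled or adjusted.

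Under Secondary outcomes related to surgical and postsurgical parameters, two times are treated differently: "Total procedure time as well as normalized to number of spinal levels from the upper to the lower instrumented vertebra", and "Instrumentation time normalized to number of levels".

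Under Sample size for secondary objectives, the protocol suggests that the dose difference might be two-fold and adds: "The study will be sufficient to identify differences down to 20% between navigated and free hand when the navigated and free hand groups are pooled", at 80% power and alpha 0.05. No SD or coefficient of variation (CV) of dose is given.

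The Statistical analysis section says that for continuous variables in two independent groups the "Student’s t-test for uncorrelated means will be used". It also mentions regression for dependency between variables, without naming dose, levels or age.

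The inclusion criterion on age is "Age 12 years and older", with no upper limit. Randomisation is stratified by operating theatre only.

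**The concern.** The navigated procedures and the verification scan image the region to be instrumented, so the extent imaged, and with it the dose, plausibly grows with the construct. Dose plausibly also differs between a 12-year-old and an older adult. Under an unadjusted t-test, all of that between-patient variation stays in the error term. With about 22 patients per arm, and neither factor balanced by the design, the confidence interval for the dose contrast is probably wider than it needs to be.

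The stated target is also relative (20%, two-fold), whereas a t-test on mSv estimates an absolute difference. At stake is how well the trial can resolve a modest dose difference in one of its main domains.

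**Working it through.** **Inputs from the protocol.** Detectable difference 20%, power 80%, alpha 0.05 (Sample size for secondary objectives; sidedness is not stated there, and two-sided is assumed here). About 22 patients per arm (Sample size for primary objective). Pooled groups of 44 navigated and 44 free hand are stated for the SRS-22r; three arms of 22 would give 44 against 22. Both are shown.

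**Not in the protocol, so assumed.** The CV of dose, and the multiple correlation ρ of age and planned levels with dose.

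**Step 1: the plan's own figure.** The 20% cannot be reproduced without an SD. It can only be inverted to find the CV that it needs:

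CV = 0.20 / [(1.960 + 0.842) × √(1/n₁ + 1/n₂)]

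- 44 v 44: 0.20 / (2.802 × 0.2132) = 0.335; with the t distribution, 0.331.
- 44 v 22: 0.20 / (2.802 × 0.2611) = 0.273; with the t distribution, 0.269.

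On the log scale, a 20% reduction is |ln 0.80| = 0.223. The t-based standardised differences are 0.20/0.331 = 0.604 and 0.20/0.269 = 0.743. The log-SD may therefore be at most 0.223/0.604 = 0.369 (44 v 44) or 0.223/0.743 = 0.300 (44 v 22).

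**Step 2: effect of adjustment.** The residual SD is SD × √(1 − ρ²), so the standardised difference grows by 1/√(1 − ρ²). For ρ = 0.5 that factor is 1/0.866 = 1.155. The few degrees of freedom spent on covariates are ignored. Power for a 20% difference (t-test, two-sided 0.05):

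| ρ (assumed) | CV exactly at the limit | CV 0.331, 44 v 22 | CV 0.50, 44 v 22 |
|---|---|---|---|
| 0 (unadjusted) | 80% | 63% | 33% |
| 0.2 | 82% | 64% | 34% |
| 0.3 | 84% | 67% | 35% |
| 0.4 | 86% | 70% | 38% |
| 0.5 | 90% | 75% | 41% |
| 0.7 | 97.5% | 89% | 56% |

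The first power column is the same for 44 v 44 and 44 v 22 to the precision shown, because each starts from its own CV limit.

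**Step 3: if the difference is two-fold.** Take it as a halving from the higher mean, with CV 0.50. The standardised difference is 0.50/0.50 = 1, and unadjusted power with 44 v 22 is about 96%. Adjustment then changes little.

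**The case against.** The strongest objection is that covariates and transformation for one secondary outcome are usually left to a statistical analysis plan, which is not shown here. Total effective dose per procedure is also a legitimate, patient-relevant quantity. Both are true, so nothing here counts as an error in the outcome definition. The article does, however, name a default test and a sensitivity claim for dose, and the efficiency of that test for that claim can be judged from the text.

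Several stronger readings are tempting and are not supported:

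- A reader might infer that the plan rules out any account of age or levels. It does not. Regression is listed generically, no test is tied to dose by name, and dose is split by fluoroscopy and by scan.
- A reader might infer that because times are scaled by level, dose should be too. The protocol gives no reason for scaling the times, and dividing dose by levels would change the quantity estimated without necessarily gaining precision.
- A reader might infer that a chance imbalance in age or levels biases the contrast. Under randomisation it is part of the sampling error that the confidence interval already reflects.
- A reader might infer that the 20% figure is wrong. This point does not show that. The power gains start from a CV chosen to give 80%, so they illustrate the mechanism only.

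One practical objection stands. The levels mentioned for the times read as those actually instrumented. Table 2 lists preoperative planning as a data source but does not name planned levels.

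**Conclusion.** The point holds as a minor, low-cost improvement. The default comparison of patient dose is unadjusted and in raw mSv, and it probably gives up precision for the 20% target. The gain rests on an assumed correlation of age and planned levels with dose. It is slight at 0.2 to 0.3 (80% to 82–84%), useful at 0.4 to 0.5 (86–90%) and large only at 0.7 (97.5%), all from a starting point where the 20% claim is just met. If the true CV is well above 0.27 to 0.33, adjustment helps but does not rescue the claim: at CV 0.50 with 44 v 22, power stays at or below 56% over the range examined. For a two-fold difference the consequence is small.

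**What to change.** Specify that effective dose is compared between arms on the log scale, in a linear model on arm, age and the number of levels planned before randomisation. Report the ratio of geometric means with its 95% CI, which matches the relative target in the sample size section. Keep raw mSv as descriptive results.

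Take the number of levels from the preoperative planning record. The levels finally instrumented may be settled after the intraoperative randomisation and could be affected by the arm. State the CV of dose behind the 20% statement so that the target can be checked.

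The cost is a change of analysis wording. Age should be available from the demography collected at the first visit; planned levels may have to be extracted from the planning record. The effect becomes a ratio, so mSv values must be shown beside it for clinical readers.
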